#### Fidelity Monitoring

2.5.2

The plan for assessing fidelity is informed by Garbacz et al. (2014) and developed based on procedures associated with Triple P (e.g., Sanders et al. 2020), which includes measures of content fidelity (e.g., post‐session checklists, dosage, training providers) and process fidelity (e.g., process quality measure; Kirby and Sanders 2014). A post‐session checklist, similar to those used with Triple P and other evidence‐based interventions (Sanders et al. 2020), will be completed by the parent coaches after each session to determine whether the intended content was presented to participants. A separate team member will then review a randomly selected sample of recordings (25%) to provide a second assessment of content fidelity. Process fidelity will be assessed using the process quality measure and will also be completed for a random sample of sessions (25% of sessions).

#### Intervention Outcomes

2.5.3

To assess preliminary intervention effects, this study will use a combination of validated parent‐report scales and objective measures to evaluate child and parent outcomes across three timepoints (T1–T3). Main child outcomes include social‐emotional functioning, sleep, physical activity, and sedentary behavior. Social‐emotional functioning will be measured using the strengths and difficulties questionnaire (Goodman 1997). Sleep, physical activity, and sedentary behavior will be measured using axivity accelerometers worn on the nondominant wrist for 7 consecutive days. Sleep variables (e.g., duration, quality) and physical activity variables (e.g., average minutes of sedentary, light, and moderate physical activity) will be derived using validated algorithms, such as the L512 algorithm within GGIR; Van Hees et al. 2015), and using age‐appropriate cut‐points (Migueles et al. 2019). We will assess the acceptability of the accelerometers by evaluating the number of full days (or nights) of wear data provided by each child. Secondary parenting outcomes will include parenting practices, ethnic‐racial socialization behaviors and attitudes, and parenting self‐efficacy. Each measure is described in Table 3, including psychometric properties and language validation status (English and/or Spanish). Measures not available in Spanish (i.e., parent–child sleep interactions scale, racial socialization competency scale) will be translated by bilingual study team members or a professional service using recommended procedures. This includes forward and back‐translation, reconciliation of discrepancies, and pilot testing to ensure cultural and linguistic appropriateness. This pilot study will also serve as an opportunity to examine the reliability and validity of these translated measures within our Spanish‐speaking sample.

#### Demographics and Other Covariates

2.5.4

We will collect various demographic measures (at T1) and relevant covariates that have been shown to impact key study outcomes (T1–T3). Demographic measures will include characteristics such as parent and child gender, race/ethnicity, preferred language, years lived in the United States, age, and socioeconomic factors. Other covariates will include measures of parents' perceived discrimination (everyday discrimination scale; Williams et al. 1997), ethnic/racial identity (multidimensional inventory of black identity; Sellers et al. 1998), and childhood adversity exposure (expanded ACEs; Cronholm et al. 2015). These demographic and sociocultural factors have been consistently shown to be associated with parenting and child health (e.g., parent ACEs with harsh parenting; Wattanatchariya et al. 2024; parental discrimination and ethnic identity with ethnic‐racial socialization practices; White‐Johnson et al. 2010; socioeconomic status with child physical activity and behavioral problems; Gautam et al. 2023), and will therefore be examined as potential covariates or moderators in our analyses.

### Data Collection

2.6

We plan to promote participant retention by offering an escalating compensation schedule (i.e., $75, $100, $125, for a total of $300) and encouraging participants to continue with assessments even if they drop out of the intervention. We will also send reminder emails or texts about session content, homework, and appointment dates. Each participant will be assigned a point person (a member of the research team) who will be available for questions via text throughout their time in the study. All survey assessments will be completed and stored using Qualtrics. To maintain confidentiality, only select members of the study team will have access to Qualtrics. The data will be cleaned and deidentified before completing statistical analyses.

### Data Monitoring

2.7

Because of the low‐risk status of this pilot study, the data and safety monitoring plan for this trial focuses on close monitoring by the study principal investigator (PI), along with prompt reporting of excessive adverse events and any serious adverse events to the NIH and to the IRB at the University of South Carolina. The PI will monitor collective injury and other adverse event rates across all participants quarterly. If a larger than reasonably expected adverse event rate should occur—such as incidents of undue psychological distress, family conflict, or exacerbated child behavior problems resulting from intervention content as reported by parents—then the PI will comply with reporting requirements with respect to the IRB and NIH, as well as any potential actions regarding the stopping (or modifying) of the trial. Additionally, any protocol modifications will be communicated to the IRB and updated in the clinical trial registry.

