### Study Setting and Design

2.1

Because the protocol will be implemented virtually, families living anywhere in the state of South Carolina will be able to participate. To pilot the feasibility of the ROOTS program, the study will use a longitudinal two‐arm randomized control trial design in which families are randomized into a parenting intervention (*n* = 30) or a control (*n* = 30) condition on a 1:1 ratio. We selected a nutrition control condition that is a similar length (6 weeks) and provides a similar structure (offers parents new strategies and a workbook to reflect on their progress and goals). This decision was based on empirical evidence suggesting a need for alternative approaches to intervention research to maximize participant engagement and minimize ethical concerns related to withholding services from underserved populations (Henry et al. 2017). Assessments will occur at three timepoints: pre‐intervention (T1), post‐intervention (T2), and 3‐month follow‐up (T3). After completing the third assessment, each condition will have the opportunity to receive the materials from the other condition.

The hybrid effectiveness‐implementation approach adopted for this study examines intervention outcomes while concurrently assessing barriers and facilitators related to successful program delivery (see Figure 1). Blinding will occur at several levels, primarily with participants, outcome assessors, and data analysts. For example, intervention participants will not be aware of which intervention group is considered the treatment or control; rather, they will be instructed that the study seeks to compare the effects of two health interventions. Outcome assessment will be conducted using Qualtrics, which prevents potential bias from using unblinded assessors. Blinding will also occur at the data analyst level, specifically related to assessing outcomes.

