### Participants

2.2

Eligible parents must (a) live in South Carolina, (b) be able to speak English or Spanish, (c) have access to a device to be able to attend Zoom video calls, and (d) must not have received any parent training services or health services aimed at improving their children's behaviors or lifestyle habits, such as sleep or physical activity promotion programs, in the 12 months before enrolling in the study. Parents must also be the primary caregivers of a child that (e) is between 3 and 6 years of age, (f) is Black/African American or Latiné/Hispanic, and (g) their child must not have any psychological or chronic health issues that significantly interfere with their communication (e.g., child does not understand basic instructions from their parent) or that limit their ability to engage in physical activity (e.g., child uses a wheelchair). Primary caregiver refers to a parent who resides in the same household as the child for at least 50% of the time and has primary custody of the child. We chose to include children with physical or mental health diagnoses as long as these issues did not interfere with key intervention targets, such as their ability to benefit from parenting strategies and adjust their lifestyle behaviors (e.g., physical activity level). These criteria were selected because they align with our universal prevention approach that targets families across the risk spectrum. Target recruitment for this study is 60 families (*n* = 30 experimental, *n* = 30 control).

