#### Program Interventionists

2.4.4

Interventionists will be community‐integrated professionals (e.g., school counselors, community health workers) selected based on their shared cultural backgrounds with participants and prior experience working with families. These interventionists will also serve as designated recruiters for the study (described above). All interventionists will complete formal Triple P training (i.e., Standard Level 4 4‐day virtual training) and additional ROOTS‐specific training. This training will include: (a) reviewing the ROOTS facilitator manual, (b) viewing video demonstrations of each session led by the PI with a practice family, (c) participating in live role‐plays and supervision, (d) completing post‐session fidelity checklists where they self‐rate their coverage of topics, and (e) receiving ongoing consultation with the PI, consistent with the Triple P training model (Sanders et al. 2020).

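### The only stated periodic review of adverse event rates pools both arms, although its trigger concerns harm from intervention content; counts should also be tabulated by arm.

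*Protocol article*

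**What the plan says.** Data Monitoring (2.7) puts safety oversight with the PI. The quantity reviewed is named: "The PI will monitor collective injury and other adverse event rates across all participants quarterly". The condition for action follows: "If a larger than reasonably expected adverse event rate should occur". Its examples are psychological distress, family conflict and worse child behavior, qualified as "resulting from intervention content as reported by parents". If the condition is met, the PI reports to the IRB and NIH and considers changing or stopping the trial. No expected rate, numerical threshold or review by arm is given. A separate route does not depend on this condition in the case of serious events: the plan provides for "prompt reporting of excessive adverse events and any serious adverse events to the NIH and to the IRB".

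Study Setting and Design (2.1) randomizes families to each "condition on a 1:1 ratio", 30 and 30, and Participants (2.2) gives the total: "Target recruitment for this study is 60 families". Section 2.1 names participants, outcome assessors and data analysts as the main blinded groups. The PI is not named there, and the training of ROOTS interventionists includes "receiving ongoing consultation with the PI" (Program Interventionists, 2.4.4).

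**The concern.** The metric and the trigger do not match. Harm from content belongs to the arm that received the content, and the two arms differ in just that respect: ROOTS covers racial pride, preparation for bias and discipline strategies in live sessions with role play, while control is a self-directed nutrition workbook. A collective rate averages over the difference that the trigger is about.

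The pooled rate also gives up the one internal benchmark. Because no expected rate is stated, the concurrent control arm is the only reference inside the trial for how often family conflict or child behavior problems would be reported anyway. Merging the arms removes that reference.

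A related problem is ascertainment. ROOTS parents have six live sessions of 60 to 90 minutes with a coach. Control parents have a study point person reachable by text (Data Collection, 2.6) but no sessions. More events may come to notice in ROOTS simply because there is more conversation, and a pooled rate would not show that either. The documents do not establish that this happens; it is plausible from the difference in contact.

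**Working it through.** The documents give no adverse event rate or alarm threshold, so there is no safety figure of theirs to reproduce. The sample size agrees: 30 + 30 = 60.

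**Dilution.** Let pT be the proportion of ROOTS families with an event and pC the proportion in control.

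- Pooled rate = (30·pT + 30·pC) / 60 = (pT + pC) / 2.
- Pooled excess over background = (pT + pC) / 2 − pC = (pT − pC) / 2.

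A one-arm excess is therefore exactly halved. Assumed example: pC = 5% and pT = 25% gives (25 + 5) / 2 = 15%, so a 20-point excess appears as 10 points. The same 15% would arise if the arms were reversed, or if both arms ran at 15%. The pooled figure cannot distinguish these three cases.

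**What dilution costs in detection.** All rates here are assumptions. Each family counts at most once, all 60 are enrolled, and the background rate is treated as known. The alarm is the smallest count whose exact binomial probability under the background rate is at most 0.05, computed once for all 60 families and once for the 30 ROOTS families.

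| Background | Alarm count, pooled (false-alarm prob.) | Alarm count, ROOTS arm (false-alarm prob.) |
|---|---|---|
| 2% | 4 of 60 (0.032) | 3 of 30 (0.022) |
| 5% | 7 of 60 (0.030) | 5 of 30 (0.016) |
| 10% | 11 of 60 (0.034) | 7 of 30 (0.026) |

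Probability of an alarm when the excess is in ROOTS only:

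| Background | ROOTS excess | Excess seen when pooled | Pooled | ROOTS arm alone | Loss from pooling |
|---|---|---|---|---|---|
| 2% | +10 points | +5 | 0.617 | 0.715 | 0.098 |
| 2% | +20 | +10 | 0.948 | 0.974 | 0.026 |
| 2% | +30 | +15 | 0.997 | 0.999 | 0.002 |
| 5% | +10 | +5 | 0.393 | 0.476 | 0.083 |
| 5% | +20 | +10 | 0.826 | 0.902 | 0.076 |
| 5% | +30 | +15 | 0.977 | 0.992 | 0.015 |
| 10% | +10 | +5 | 0.282 | 0.393 | 0.111 |
| 10% | +20 | +10 | 0.683 | 0.840 | 0.157 |
| 10% | +30 | +15 | 0.927 | 0.983 | 0.056 |

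The loss runs from 0.002 to 0.157, about 0 to 16 percentage points. The ROOTS-arm alarm has the lower false-alarm probability at every background rate, so its advantage does not come from a looser threshold. These alarm counts illustrate the cost of pooling; they are not proposed as rules for the trial.

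**Size of a quarterly table.** The recruitment benchmark is 60 families in 12 months. If recruitment were even, that is 60 / 4 = 15 families per quarter, or 7.5 per arm. Early by-arm counts would be very small, and the detection figures above apply only near full enrollment.

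**The case against.** The strongest objection is that the trial can already trace harm in other ways. A reader might infer from the pooled rate that no event can be attributed to ROOTS. The text does not support that: its examples are events that parents themselves link to content, serious events are reported whatever the rate, and nothing stated prevents the PI from looking up a family's arm. This stands, and it confines the point to the rate. It does not remove the point. Parents are told only that two health interventions are being compared, so a report about content can come from either arm, and one parent's judgment of one event is weaker evidence than a randomized comparison.

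A reader might also infer that harm is never compared between arms. That too goes beyond the documents. The SDQ and the Parenting Scale are collected in both arms at T1 to T3 and modeled with a time-by-group term, so worse child behavior or harsher discipline under ROOTS could show there. This stands in part: that analysis is not the quarterly review, and it does not count adverse events.

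Third, control parents are not without a reporting channel, since every participant has a point person. This stands; contact remains unequal but is not absent.

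Fourth, the wording could mean only that everyone is covered, and the full monitoring plan, which is not shown, may tabulate by arm. That is possible. However, the article goes beyond silence: it names the quantity monitored, and the natural reading is one pooled rate.

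Finally, this is a low-risk pilot with few expected events. That limits the gain but hardly affects the cost of the change.

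**Conclusion.** The point holds for the rate review. The only stated periodic review of adverse event rates uses a collective figure that halves an excess confined to ROOTS and cannot by itself say which arm the excess comes from, while the trigger concerns content. The halving follows from the 1:1 allocation alone. The detection cost is modest and rests on assumed background rates, a known background, one event per family and full enrollment. The documents do not support a claim that harm from ROOTS would go unseen. Review by arm breaks no stated blind, because the PI is not listed as blinded and already consults with the ROOTS coaches.

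**What to change.** - State in Data Monitoring that adverse events are tabulated by arm as well as overall, cumulatively, at each quarterly PI review and in the final report.
- Ask both arms the same adverse-event question in the T2 and T3 Qualtrics surveys, and show separately any events known only through coach contact, so that unequal contact is not mistaken for unequal harm. If some of these assessments are already complete, add the question to those that remain and report the earlier ones separately.
- Keep the by-arm table from the blinded data analysts; they can work from outcome data that exclude it.

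The cost is an extra column in an existing review and one survey item, with no added staff or visits. The downside is small counts, especially in early quarters. The table should be labeled descriptive and not used for formal testing.

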#### Program Format and Delivery

2.4.3

ROOTS consists of 6 weekly one‐on‐one sessions, each lasting approximately 60–90 min. Sessions follow a structured format that includes a review of homework activities, didactic teaching, interactive discussions, and role play. Parents meet virtually via Zoom in either English or Spanish, depending on their preference. Sessions are led by trained interventionists who match the racial and ethnic backgrounds of participants. Parents receive a ROOTS toolkit by mail, which includes a workbook, culturally relevant children's books to support ethnic‐racial socialization, a program schedule, and study‐branded materials (e.g., handheld fan, hand sanitizer). Participants also receive weekly text message reminders about homework and appointment dates.

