#### Nutrition Control Condition

2.4.5

Parents in the active control condition will receive a six‐session self‐directed nutrition intervention based on best practices for healthy eating. These materials were compiled from Myplate.gov and Nibbles for Health and cover a range of topics, including nutrition basics, trying new foods, breakfast and snacks, fruits and vegetables, protein and dairy, and bread and grains. Parents are given a workbook that includes empty spaces for goal setting and behavior tracking, as well as a study overview schedule and study swag. After the 3‐month follow‐up assessment (T3), parents in the nutrition control condition will receive the parenting intervention materials and have the option to attend a 1‐h consultation session to provide an overview of the materials.

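### The harms named in the adverse-event trigger depend on parents blaming intervention content, and the arms differ in live contact, so adverse-event counts would be a biased basis for judging excess harm in ROOTS

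*Protocol article*

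**What the plan says.** Protocol article, Data Monitoring (2.7): "The PI will monitor collective injury and other adverse event rates across all participants quarterly". The action clause opens "If a larger than reasonably expected adverse event rate should occur" and then gives, as examples, "undue psychological distress, family conflict, or exacerbated child behavior problems resulting from intervention content as reported by parents". Reporting to the IRB and NIH follows, together with possible modification or stopping of the trial. Serious adverse events are to be reported promptly in any case. The section gives no expected rate and describes no comparison by arm.

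Program Format and Delivery (2.4.3): "ROOTS consists of 6 weekly one‐on‐one sessions, each lasting approximately 60–90 min", held on Zoom with a trained interventionist.

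Nutrition Control Condition (2.4.5): "Parents in the active control condition will receive a six‐session self‐directed nutrition intervention based on best practices for healthy eating". The control arm's only consultation is optional, lasts one hour and comes after T3.

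Data Collection (2.6) gives every participant, in either arm, a research-team contact who can be texted with questions throughout the study. Study Setting and Design (2.1) puts both arms through the same T1, T2 and T3 assessments.

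**The concern.** As worded, a named harm has to pass two filters: the parent must notice it, and the parent must put it down to the content received. The second filter is unlikely to act equally in the two arms. A family quarrel is easier to blame on sessions about discipline and preparing a child for bias than on a nutrition workbook. The occasions for a harm to surface differ as well: six one-to-one conversations in one arm, and none before T3 in the other.

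A judgement that a rate exceeds expectation needs a background rate. In a randomised trial the control arm is the natural source, and attribution-filtered, unevenly prompted counts spoil it for that use. An apparent ROOTS excess could be ascertainment alone, and a real excess could be dismissed as ascertainment. The study is meant to justify larger trials (Current Study Aims, 1.3), so its harm data will be carried forward.

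**Working it through.** The article states no expected adverse-event rate, threshold or reporting fraction, so there is no figure to reproduce. The calculations below only illustrate direction and range.

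**Inputs from the article.** 30 families per arm; six live sessions in ROOTS against none in control before T3; rates monitored pooled over both arms.

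**Assumptions, not in the article.** The same true event risk in both arms, and a probability that an event is reported which is higher in ROOTS.

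**Expected counts.** Expected reports per arm = 30 × true risk × reporting fraction. With equal true risk, the apparent rate ratio is the ratio of the reporting fractions.

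| True risk, both arms | Reporting, ROOTS / control | Expected reports | Apparent ratio |
|---|---|---|---|
| 10% | 0.8 / 0.6 | 2.4 / 1.8 | 1.3 |
| 10% | 0.8 / 0.3 | 2.4 / 0.9 | 2.7 |
| 20% | 0.9 / 0.6 | 5.4 / 3.6 | 1.5 |
| 20% | 0.9 / 0.3 | 5.4 / 1.8 | 3.0 |

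**Chance that ROOTS shows more events than control.** Exact binomial counts, n = 30 per arm, true risk 20% in both arms:
- reporting 0.9 in both arms: 0.43 (below 0.5 because ties are possible)
- 0.9 against 0.6: 0.68
- 0.9 against 0.3: 0.90

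**Pooling.** If the true risk were 10% in control and 30% in ROOTS, the pooled rate would be (10% + 30%) / 2 = 20%. The pooled figure cannot show which arm the events come from.

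**What equal ascertainment would buy.** Normal-approximation power, two-sided 5%, 30 per arm: about 19% for 10% against 20%, and about 49% for 10% against 30%. Even well-collected counts would remain descriptive.

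**Which named harms have another measure (Table 3).**
- Worsened child behavior: yes. The SDQ covers conduct problems and emotional symptoms in both arms at T1 to T3.
- Family conflict: only in part. The parent–child sleep interactions scale touches sleep conflict, and the Parenting Scale covers over-reactive discipline.
- Parent distress and general family conflict: no listed outcome measure.

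**The case against.** The strongest reply is that the attribution wording only illustrates. It follows an open-ended lead-in, and the same section monitors injuries and other adverse events, and reports serious ones, with no attribution condition. This stands. A reader might infer that only harms blamed on content count, or that distress from the questionnaires or the wrist device is excluded. The text does not say so. Distress at T1 also precedes randomisation and has no bearing on whether ROOTS causes harm.

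Second, the section plans pooled oversight, not a comparison by arm, and claims no causal inference from counts. This also stands as a description. It does not rescue the counts, because a pooled rate set against an unstated expectation cannot locate an excess in ROOTS either.

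Third, controls are not cut off. They have the text contact and the same online assessments, and nothing says that coaches collect adverse events. That sessions would bring out more reports is an inference from contact time. The text contact narrows the imbalance, but it is offered for families' questions and is not described as asking about harms.

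Fourth, adverse-event forms and their schedule may sit in the full monitoring plan, so their absence from an article is no finding. This is accepted. The point rests on the published wording, which builds attribution into the description of the named harms.

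Finally, it is tempting to conclude that the trial cannot show whether ROOTS causes harm. That goes too far: the SDQ, the sleep interactions scale and the Parenting Scale are collected identically in both arms without any attribution.

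**Conclusion.** The point holds in a limited form. The harms most plausible for a parenting program are described by what parents attribute to content, the arms differ clearly in live contact, and rates are pooled against an unquantified expectation. Adverse-event counts collected on that basis would be a biased guide to excess harm in ROOTS. The gap matters most for parent distress and general family conflict, for which the counts are the only described source.

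The size is unknown. The range of about 1.3 to 3 for a spurious rate ratio rests wholly on assumed reporting fractions, and in absolute terms it is a difference of 0.6 to 3.6 expected events (2.4 − 1.8 to 5.4 − 1.8). The change is worth making because it is cheap and improves the safety record. It does not show that the trial is unsafe or that its outcome comparisons fail.

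**What to change.** 1. In section 2.7, replace the attribution phrase with events *occurring during study participation, whatever the suspected cause*, and record suspected relatedness as a separate field, not as a condition of entry.
2. If the full monitoring plan does not already do so, add the same short set of items to the T2 and T3 Qualtrics surveys in both arms: parent distress, family conflict, worsened child behavior and injury since the last assessment.
3. Tabulate these solicited events by arm, descriptively. List events volunteered to coaches or the text contact separately.

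**Cost.** One reworded sentence and about four items on two existing surveys. More unrelated background events will be recorded in both arms. With 30 per arm the comparison stays descriptive. Recruitment began in May 2024 and follow-up is expected to finish at the end of fall 2025, so families already past T2 or T3 cannot be asked again on schedule. The report should state this as a limitation.
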